### Subgroup analysis

In order to look at associations according to admission diagnosis, sex and age, the results will be analyzed separately for female patients, surgical patients with a cardio-vascular admission diagnosis, patients who only had a low propofol-associated energy intake during the first 48 hours after ICU admission (daily propofol-associated energy intake (level I): < 1.5kcal/kg per day), patients younger than 65 years and patients with an admission APACHE II score ≥ 25.

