## INTRODUCTION

Recently, controversy has arisen regarding whether propofol has undesirable side effects compared to other sedative drugs.^(1)^ These effects may mainly occur in patients over 65 years of age,^(2)^ but have also been observed in pediatric populations.^(3)^ A meta-analysis by Kotani et al.^(1)^ involving 252 randomized controlled trials and more than 30,000 patients found that the use of propofol is associated with a potential 10% increase in mortality compared with other sedation strategies. This fatal side effect may also be relevant for critically ill patients, for whom there was a 10% relative increase in mortality (15% *versus* 13%), with a Bayesian approach indicating a 75.7% probability of harm.^(4)^

In contrast, other meta-analyses have found that, compared to midazolam, the use of propofol does not worsen the outcome for a heterogeneous population of critically ill adult patients,^(5)^ and may even reduce the length of stay in the intensive care unit (ICU), the duration of mechanical ventilation (MV) and the time to extubation for acutely ill surgical patients.^(6)^ Two recent meta-analyses compared propofol with dexmedetomidine. On the one hand, there was no difference in mortality.^(7,8)^ However, in the meta-analysis by Heybati et al.,^(7)^ for example, mortality was only an endpoint in four trials involving 364 patients. This small sample size may have contributed to the very low certainty of these negative results. Conversely, Heybati et al.^(7)^ found that propofol may increase the duration of MV and lengthen hospital stays for unselected patients, as well as increasing the risk of ICU-associated *delirium* in cardiac surgery patients.

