### Selection of the study population

#### Inclusion criteria

Patients selected from the database will be aged 18 years or over and have a body mass index (BMI) of over 13kg/m^2^. Other inclusion criteria will be an ICU length-of-stay (LOS) of > 48 hours. The rationale behind this inclusion criterion is that the potentially detrimental effects of propofol on survival are not attributable to immediate or acute reactions, but instead require more than 48 hours of therapy to manifest (e.g., in the event of propofol infusion syndrome).^(1,14)^

For patients admitted to the same unit during the same hospital stay, we will only analyze the first ICU admission. Patients readmitted after hospital discharge will be included as separate cases.

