#### Sample size considerations

The large number of patients in the database (more than 18,000 with an ICU LOS > 2 days) will be sufficient to support advanced, in-depth statistical analyses. In this subgroup, the 60-day hospital discharge alive rate is approximately 70%, resulting in more than 10,000 events (discharges).^(15)^ Considering the number of planned predictor parameters (confounders, see below), the events per predictor parameter ratio will be large enough to perform reliable complex statistical analyses.^(16)^

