### Confounder variables

The list of confounder variables is presented in table 1. To account for heterogeneity across ICUs, all models will include random effects for each unit.

**Table 1 t1:** List of confounder variables. In addition to these variables, all models will contain a random intensive care unit variable

Variable	Time of recording
Number of days on oral nutrition	Days 0 - 2 post ICU admission
Number of days on parenteral nutrition	Days 0 - 2 post ICU admission
Number of days with protein intake > 1.2g/kg day	Days 0 - 2 post ICU admission
Year of therapy	Admission date
APACHE II score	ICU admission
Main admission diagnosis*	ICU admission
Admission category (surgical elective/emergency, medical)	ICU admission
Age	ICU admission
Sex	ICU admission
BMI	Pre-ICU admission
Baseline number of days under MV†	Days 0 - 2 post ICU admission
Number of days under MV before state transition‡	Days 0 - 11 post ICU admission

ICU – intensive care unit; APACHE - Acute Physiology and Chronic Health Evaluation; BMI - body mass index; MV - mechanical ventilation.

* Gastrointestinal, cardio-vascular, metabolic, neurologic, orthopedic/ trauma, renal, pulmonary, sepsis, other. Sepsis was the main admission diagnosis, if there was an infection-associated circulatory dysfunction requiring vasopressor therapy which dominated dysfunction of other organs;

† only used when analyzing the association of daily propofol-associated energy intake (categorized variable) with time-to-discharge alive/in-hospital death (cumulated for the early and late phase after intensive care unit admission);

‡ only used in multistate models

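### The subgroup plan aims to look at associations by diagnosis, sex and age but analyses one side of each, and patients aged 65 or over get no analysis of their own

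*Protocol article*

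**What the plan says.** The protocol article's Subgroup analysis section gives its purpose and method in one sentence: "In order to look at associations according to admission diagnosis, sex and age, the results will be analyzed separately for female patients". The list continues with "surgical patients with a cardio-vascular admission diagnosis", then patients with low propofol-associated energy intake in the first 48 hours, and ends with "patients younger than 65 years and patients with an admission APACHE II score ≥ 25". No stratum of men, of patients aged 65 or over, of the remaining diagnoses, or of APACHE II below 25 is named.

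The Introduction says of undesirable effects of propofol: "These effects may mainly occur in patients over 65 years of age". It adds that they have also been seen in children.

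Older patients are in the cohort: "Patients selected from the database will be aged 18 years or over", with no upper limit. Age, sex, admission diagnosis, admission category and APACHE II enter the models as adjustment variables (Confounder variables: "The list of confounder variables is presented in table 1"). No term that lets the propofol association differ by any of them is described.

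**The concern.** The aim given for the subgroups is to see how associations vary by diagnosis, sex and age. That is a question about differences between strata, and fitting one stratum per factor does not answer it. Adjusting for age or sex as a confounder does not answer it either, because adjustment assumes one propofol association common to all ages and both sexes.

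For age, the stratum chosen is also the opposite of the one the Introduction points to. If the association is near null under 65 and adverse above it, the only age-specific result would be the null one, and a reader could take it as reassurance. Conversely, a reader could take a small gap between the under-65 and overall results as an age effect, although no interval for that gap is planned. The study's general aim is evidence on safe dosing and duration, so older patients are a stratum that readers will look for.

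**Working it through.** **1. Stated aim against named strata**

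| Factor in the stated aim | Stratum named | Complement named | Between-stratum comparison |
|---|---|---|---|
| Admission diagnosis | surgical cardio-vascular | no | none |
| Sex | female | no | none |
| Age | under 65 | no | none |

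APACHE II of at least 25 is also one-sided, but severity is not in the stated aim. The low-intake subgroup is defined by early exposure and is a separate matter.

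**2. What the planned age comparison can show**

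Let b_old and b_young be the log hazard ratios in the two age strata, and s the share of statistical information from patients aged 65 or over. Approximately:

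- overall = s × b_old + (1 − s) × b_young
- overall − b_young = s × (b_old − b_young)

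The visible gap is therefore only the fraction s of the true difference. The documents do not give s, so I assume 30-50%. With hazard ratios of 1.20 at 65 or over and 1.00 below (illustrative, also not in the documents), the overall hazard ratio is exp(s × ln 1.20):

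| s | Overall | Under 65 (planned) | 65 or over (not planned) |
|---|---|---|---|
| 0.3 | 1.056 | 1.00 | 1.20 |
| 0.4 | 1.076 | 1.00 | 1.20 |
| 0.5 | 1.095 | 1.00 | 1.20 |

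**3. Does sample size explain the omission?**

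Sample size considerations gives "more than 18,000 with an ICU LOS > 2 days" and about 70% discharged alive. This reproduces its event count: 18,000 × 0.70 = 12,600, consistent with the stated figure of more than 10,000 discharges. The other 18,000 − 12,600 = 5,400 patients died or were censored, so deaths number at most about 5,400. If 20% died (assumed), there are 3,600.

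For one two-level intake contrast with a proportion q at one level and E events in total:

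- SE of the log ratio of hazard ratios = √[1/(E·s·q(1−q)) + 1/(E·(1−s)·q(1−q))]
- ratio detectable with 80% power at two-sided 5% = exp[(1.96 + 0.84) × SE]

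Here s is the share of events at 65 or over. With s = 0.3-0.5 and q = 0.2-0.5 (both assumed):

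| Outcome | E | Detectable ratio of hazard ratios |
|---|---|---|
| Discharge alive | 12,600 | 1.105-1.146 |
| Discharge alive, stated floor | 10,000 | 1.119-1.165 |
| Death, upper bound | 5,400 | 1.165-1.231 |
| Death, if 20% | 3,600 | 1.205-1.290 |

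One line in full: E = 12,600, s = 0.3 and q = 0.2 give 3,780 and 8,820 events. SE = √[1/604.8 + 1/1,411.2] = 0.0486, and exp(2.80 × 0.0486) = 1.146.

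These figures are optimistic. They place every patient at one of the two levels compared and ignore confounder adjustment and ICU clustering. They also use 60-day events, whereas Outcome measures counts events only to the end of the lead time.

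**The case against.** **Expectation of harm.** A reader might infer that the protocol expects harm above 65 and leaves its one prior hypothesis untested. The documents do not support that. The Introduction reports a possibility from a cited source, and the Research question section, which concerns dose and timing, states no age hypothesis. The Introduction also mentions delirium risk in cardiac surgery patients, and the surgical cardio-vascular group does get a subgroup.

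**Never analysed.** A reader might also infer that older patients are left out. They are not: they are in every whole-cohort model. What is missing is a separate analysis.

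**Detail left to a fuller plan.** A journal article may leave interaction tests to another document. This has weight for the form of the test, but not for the strata. The section names them and fixes the method as separate analyses, and the named strata do not serve the aim in the same sentence.

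**APACHE II.** A check in the sickest patients can stand alone, since severity is outside the stated aim. This stands.

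**Size.** The older share and the hazard ratios are assumed. A pooled log hazard ratio is weighted by information rather than head count, so the share may differ between death and discharge. The planned hazard ratios are also day-specific, so no single age difference exists. This stands: the figures show a mechanism and are not a forecast.

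**Remedy.** One interaction coefficient, or an interaction with continuous age, does not fit day-specific cumulative-exposure models easily. This stands and shapes the fix.

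**Conclusion.** The point holds in limited form. Followed as written, the subgroup section cannot show whether associations differ by age or sex, or between the surgical cardio-vascular group and other patients. For age, it selects the side opposite to the one its own Introduction singles out. On the illustrative values, an association of 1.20 confined to patients aged 65 or over would appear as 1.06-1.10 overall and 1.00 in the only age subgroup planned.

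Cohort size does not explain the omission for discharge, where a ratio of hazard ratios of roughly 1.11-1.17 would be detectable under the stated assumptions. For death the contrast is less precise, at roughly 1.17-1.29, and the true figures would be larger for the reasons given with the calculation.

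No primary or secondary estimate changes. The finding rests on the text; the numbers only illustrate it.

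**What to change.** Before any outcome analysis:

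- Add the complementary strata: at least patients aged 65 or over and male patients, also the complement of the surgical cardio-vascular group and, for completeness, APACHE II below 25.
- For the prespecified pairwise intake-pattern comparisons, report both strata and the between-stratum contrast: the ratio of adjusted hazard ratios with a 95% CI, by day where the hazard ratios are day-specific.
- Label these contrasts exploratory. No directional hypothesis and no continuous-age interaction is needed.

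Cost: no new data, since the variables are already in Table 1. The five listed subgroups become nine. In the cause-specific models, six pairwise comparisons × two outcomes × four factors give 48 contrasts before any split by day. If no true differences exist, about 48 × 0.05 = 2.4 of the 95% intervals would be expected to exclude 1, which is why the exploratory label matters. The contrast intervals will be wider than the single-stratum ones, especially for death. Adding the older stratum only after outcomes have been seen would look data-driven.

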### Sensitivity analyses accounting for palliative care bias/confounding by indication

To account for palliative care bias in the multistate models and analysis of time-to-discharge alive/in-hospital death, a sensitivity analysis is required concerning patients with an early death after termination or beginning of propofol therapy (< 48 hours after the last day of propofol therapy). Palliative care bias arises if physicians modify therapy not for medical reasons but because of end-of-life decisions. Several scenarios are possible (Table 2):

**Table 2 t2:** Survey of sensitivity analyses that account for bias relating to indications and palliative care

	Primary outcome	Secondary outcome		
Outcome measures	Time-to-discharge-alive/in-hospital death	Hazard of state transition		
Exposure variables	Categorized daily propofol-associated energy intake (kcal/kg and day)	Number of days with propofol therapy preceding transition day	Cumulated amount of PAEI (kcal/kg) before state transition (initial state: propofol "yes")	Amount of daily PAEI (kcal/kg and day) on transition day (initial state: propofol "yes")
Sensitivity analyses	Use of a lag time of two days after the last day of propofol therapy	Re-definition of the absorbing state "in-ICU death" into "palliative in-ICU death" (for time courses of different daily states #1 to #9, Table 3) and "non-palliative in-ICU death" (all other state time series)	Re-definition of the absorbing state "in-ICU death" into "palliative in-ICU death" (if [PAEI on transition day minus PAEI on the day before transition day]/PAEI on the day before transition day ≥ 100%) and "non-palliative in-ICU death" (all other changes)	Re-definition of the absorbing state "in-ICU death" into "palliative in-ICU death" (if PAEI on transition day > 4.5kcal/kg day) and "non-palliative in-ICU death" (all other intake)

PAEI - propofol-associated energy intake; ICU - intensive care unit.

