### Exposure variables

–Number of days with propofol therapy preceding transition day from one clinical state to another (numeric variable), irrespective of whether a patient had propofol on transition day or not (for definition of state transitions see Figure 1)–The cumulated amount of propofol-associated energy intake (kcal/kg) (numeric variable) preceding transition day, irrespective of whether a patient had propofol on transition day or not–The amount of daily propofol-associated energy intake (kcal/kg and day) on transition day (numeric variable)–The amount of daily propofol-associated energy intake (kcal/kg and day) (categorized variable) during different phases after ICU admission. The associations of daily propofol-associated energy intake with the outcome will be cumulated for the early phase (Days 0 - 4 after ICU admission) and the late phase (Days 5 - 11 after ICU admission).

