### Sensitivity analysis for the multistate models

If it is decided to withdraw established life-sustaining therapies (e.g., MV) based on the presumed wishes of the patient (e.g., communicated by a surrogate) or the instructions of an advance directive, sedation may be changed to drugs stronger than propofol (midazolam), and opioids (morphine, etc.) are added to analgo-sedate the patient. Death usually occurs one to two days after these therapeutic changes. Consequently, in these cases, the transition from propofol to no propofol would not indicate an improvement in clinical status (as it would otherwise). To account for this bias within the transition from the state "propofol: yes" to the state "propofol: no", we will re-classify the subsequent absorbing state "in-ICU death" into "palliative in-ICU death", if death occurs one or two days after the preceding state transition (time course of states # 1 - 7, Table 3), and into "non-palliative death" in all other time courses of states.

**Table 3 t3:** Survey of time courses of different daily states used to re-define the absorbing state "in-intensive care unit death" into "palliative in-intensive care unit death" (time course of states #1 to #9) and "non-palliative in-intensive care unit death" (all other time courses)

Time course of states #	State on day x minus n (n > 2)	State on day x minus 2	State on day x minus 1	Initial state (day x)	Absorbing state (day x plus 1)
1	Any	Any	"Propofol: yes" "MV: yes"	"Propofol: no" "MV: yes"	In-ICU death
2	Any	Any	"Propofol: yes" "MV: no"	"Propofol: no" "MV: no"	In-ICU death
3	Any	Any	"Propofol: yes" "MV: yes"	"Propofol: no" "MV: no"	In-ICU death
4	Any	"Propofol: yes" "MV: yes"	"Propofol: no" "MV: yes"	"Propofol: no" "MV: yes"	In-ICU death
5	Any	"Propofol: yes" "MV: no"	"Propofol: no" "MV: no"	"Propofol: no" "MV: no"	In-ICU death
6	Any	"Propofol: yes" "MV: yes"	"Propofol: no" "MV: yes"	"Propofol: no" "MV: no"	In-ICU death
7	Any	"Propofol: yes" "MV: yes"	"Propofol: no" "MV: no"	"Propofol: no" "MV: no"	In-ICU death
8	Any	Any	"Propofol: no" "MV: no"	"Propofol: yes" "MV: no"	In-ICU death
9	Any	"Propofol: no" "MV: no"	"Propofol: yes" "MV: no"	"Propofol: yes" "MV: no"	In-ICU death

MV - mechanical ventilation; ICU - intensive care unit.

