If it is decided to either terminate supporting therapies or, based on the presumed wishes of the patient (e.g., communicated by a surrogate) or on an advance directive, not to start or to increase life-sustaining therapies (e.g., oxygen supply), propofol may be started for sedation. Death usually occurs one to two days after these therapeutic changes. To account for this bias within the transition from the state "propofol: no" to the absorbing state "propofol: yes", we will re-classify the subsequent absorbing state "in-ICU death" into "palliative in-ICU death", if death occurs one or two days after the preceding state transition (time course of states # 8 - 9, Table 3), and into "non-palliative death" in all other time courses of states.

For the reasons described in b), the preexisting propofol dose can be increased acutely to relieve symptoms. Therefore, when analyzing transitions to the absorbing ‘in-ICU death’ state in the combination with a certain preceding propofol-associated energy intake in the initial state, we will re-define the absorbing state "in-ICU death" into "palliative in-ICU death", if there is a significant increase of propofol-associated energy intake from one day to the other ([propofol-associated energy intake on transition day minus energy intake on the day before transition day]/energy intake on the day before transition day = > 100%), or if propofol-associated energy intake on transition day is > 4.5kcal/kg day, and into "non-palliative death" with all other changes/intake.

Consequently, depending on each patient's history, these sensitivity analyses will increase the number of possible state transitions (Figure 2) compared to the primary analysis (Figure 1).

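### The palliative-care sensitivity analysis for cumulated propofol intake does not reach deaths after propofol withdrawal, and the text and Table 2 state the intake criteria differently

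*Protocol article*

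**What the plan says.** Under Exposure variables, one multistate exposure is "The cumulated amount of propofol-associated energy intake (kcal/kg) (numeric variable) preceding transition day, irrespective of whether a patient had propofol on transition day or not". Overall design of the multistate models adds that transitions to in-ICU death are modelled by current propofol status, yes or no, and by history, which includes cumulated intake.

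The section on palliative care bias and confounding by indication says that both the multistate models and the competing risk analysis need a sensitivity analysis for "patients with an early death after termination or beginning of propofol therapy". Table 2 then gives each multistate exposure its own rule for calling an in-ICU death palliative:

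- Number of days on propofol: "for time courses of different daily states #1 to #9, Table 3".
- Cumulated intake, column headed "Cumulated amount of PAEI (kcal/kg) before state transition (initial state: propofol" (yes): "if [PAEI on transition day minus PAEI on the day before transition day]/PAEI on the day before transition day ≥ 100" per cent.
- Daily intake, also limited to initial state propofol-yes: "if PAEI on transition day > 4.5kcal/kg day".

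Sensitivity analysis for the multistate models gives the reasons. When life support is withdrawn and sedation is switched, "the transition from propofol to no propofol would not indicate an improvement in clinical status", so deaths one or two days later (courses #1 to #7) are reclassified as palliative. That paragraph names no exposure. For acute escalation, the same section gives the rise criterion and continues "or if propofol-associated energy intake on transition day is > 4.5kcal/kg day".

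**The concern.** Deaths after withdrawal are the first palliative route the article describes. Each of courses #1 to #7 has propofol on day x-1 or x-2 and none on day x, so each such death enters the propofol-no to in-ICU-death transition with a cumulated intake above zero. If these deaths are driven by end-of-life decisions, they can distort the association between cumulated intake and death from propofol-no states. The sensitivity analysis should show whether that association survives their removal. As Table 2 is written, it cannot do so for this exposure.

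The second problem is that the escalation rule appears in two forms. Under one, a death counts as palliative if either intake criterion is met. Under the other, only the criterion assigned to that exposure counts. An analyst cannot follow both, and the choice changes which deaths form the non-palliative endpoint.

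**Working it through.** The article gives no figure to reproduce here, so the check applies its stated rules to its own courses.

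**Step 1. Scope.** Exposure variables: cumulated intake covers transition days with and without propofol. Table 2: the cumulated-intake column covers initial state propofol-yes only. Table 3: courses #1 to #7 have initial state propofol-no; #8 and #9 have propofol-yes. Taken at its header, the column contains 0 of the 7 withdrawal courses.

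**Step 2. The formula, if applied more widely to match Exposure variables.** Rise = (intake on transition day - intake the day before) / intake the day before. I assume 3 kcal/kg on every propofol day; the results for #1 to #8 do not depend on that value.

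| Table 3 course | Propofol day x-1 | Propofol day x | Days-on-propofol rule | Rise rule |
|---|---|---|---|---|
| #1 to #3 | yes | no | palliative | (0 - 3)/3 = -100%, not palliative |
| #4 to #7 | no | no | palliative | (0 - 0)/0, undefined |
| #8 | no | yes | palliative | (3 - 0)/0, undefined |
| #9 | yes | yes | palliative | (3 - 3)/3 = 0%, not palliative at constant intake |

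On either reading of scope, 0 of 7 withdrawal courses are palliative for cumulated intake, against 7 of 7 for days on propofol. Course #8 is inside the column's scope, yet the ratio has no value for it.

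**Step 3. The two statements of the intake rule.** Take patients on propofol and mechanical ventilation on all three days before death. They match no Table 3 course. Intakes are illustrative, in kcal/kg, day before to transition day.

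| Intake | Rise | Table 2, cumulated | Table 2, daily | Text, joined by 'or' |
|---|---|---|---|---|
| 4.8 to 5.0 | 0.2/4.8 = +4% | no | palliative | palliative |
| 1.0 to 2.5 | 1.5/1.0 = +150% | palliative | no | palliative |
| 2.4 to 5.0 | 2.6/2.4 = +108% | palliative | palliative | palliative |
| 2.0 to 3.0 | 1.0/2.0 = +50% | no | no | no |

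In the first two rows the classification depends on which statement is followed: under Table 2 each death is palliative for one intake exposure only, and under the text for both.

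**The case against.** The strongest reply is that Table 2 does not misclassify withdrawal deaths, because its header leaves them out. Hazards are estimated separately for each transition, so a death from a propofol-no state does not enter the hazard of death from a propofol-yes state. This is right, and it rules out a stronger reading that a reader might infer: that the cumulated-intake analysis keeps every withdrawal death as non-palliative. The documents do not say so. That outcome follows only for #1 to #3, and only if the formula is used outside its labelled scope; #4 to #7 then have no value at all. The reply does not close the gap, however. The propofol-no to death transition is part of the main cumulated-intake analysis, and Table 2 lists no palliative check for it.

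Separate rules also look at least partly intended. The article describes several scenarios, pairs state sequences with the exposure that counts days, and pairs intake changes with the intake exposures. Different rules are therefore not an error in themselves, and each result can be read against its own main analysis. What is missing is a reason why withdrawal matters for days on propofol but not for cumulated intake.

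The 'or' sentence ends by referring to all other changes/intake, so it may be a compressed list of the two Table 2 rules. That is a fair reading, but the sentence as written permits the combined rule. Figure 2 is not shown and might clarify the added transitions. It would still leave Table 2's header at odds with Exposure variables.

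**Conclusion.** The point holds as a coverage gap and a conflict between text and table. For cumulated intake, none of the seven withdrawal courses can be labelled palliative, although the article sets early death after termination as a target for the multistate models and states the withdrawal reclassification without limiting it to one exposure. The two statements of the intake rule also disagree for deaths that meet exactly one of the two criteria.

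The 0-of-7 result needs no assumed intake; it follows from propofol being absent on day x. The pairs in step 3 are examples only. The article gives no count or share of in-ICU deaths that follow withdrawal, so neither the number affected nor the size of any bias can be stated. The reach is limited to sensitivity analyses of secondary outcomes; the primary outcome uses a two-day lag instead. This should be corrected before analysis, but it does not undermine the main design.

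**What to change.** 1. In Table 2, extend the cumulated-intake sensitivity analysis to propofol-no initial states and apply the article's own Table 3 courses there, so that its scope matches Exposure variables.
2. Reconcile the text under Sensitivity analysis for the multistate models with Table 2: say whether the two intake criteria are combined or split by exposure. Say also how the ratio is handled when the previous day's intake is zero.
3. Preferably, derive one palliative-death indicator per death from the patient's course and use it for all three multistate exposures. If separate rules are kept, state why.

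The cost is rewording Table 2 and two paragraphs, plus one derived variable. Somewhat fewer deaths will count as non-palliative, so intervals in these sensitivity analyses will be wider.
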